**Fig 2 pone.0319635.g002:**
[figure not shown]
Graphical overview of SpasT-SCI-T study design. Overview of the three study groups and their respective schedules for blood sample collections and clinical assessments. Group 1 (10 healthy subjects) provides a single baseline blood sample. Group 2 (20 SCI patients) and Group 3 (10 TBI patients) undergo sampling within 6 hours post-trauma, during the early follow-up phase (days 1, 3, 5, 7, and 14), and at late follow-ups (3 and 6 months). Clinical assessments include the American Spinal Injury Association (ASIA) impairment scale, Glasgow Coma Scale (GCS), Glasgow Outcome Scale (GOS), and Modified Ashworth Scale (MAS), depending on the group. These outcome measures are defined and detailed in the “Outcomes” section.

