#### Group 3: Traumatic Brain Injury (TBI) patients.

Interventions for TBI patients are tailored to intracranial trauma and are similar in structure to those for SCI patients, with modifications to address brain injury specifics. A whole-body CT scan is performed upon admission to confirm intracranial hemorrhage and exclude SCI, ensuring group specificity. Neurological status is assessed using the Glasgow Coma Scale (GCS) to document the severity of brain injury [43]. Trauma-related data, including respiratory and hemodynamic stability, renal clearance, liver function, and hemoglobin levels, are recorded. Blood sampling begins with a 4 mL venous sample collected within the 6 hours of trauma during the routine biological workup. Additional samples are obtained during the acute phase at Days 1, 3, 5, 7 and 14 to capture early biomarker dynamics. Further samples are collected during late follow-up visits at M3 and M6 to evaluate the longer-term biomarker behavior. General neurological assessments are performed at M3 and M6 to evaluate recovery. These outcomes are correlated with sodium channel fragment levels to explore potential biomarker-based prognostication.

For SCI and TBI patients (Groups 2 and 3), detailed records of all medical treatments administered during hospitalization will be maintained. This includes, but is not limited to: anticoagulation therapy, antibiotic regimens, anti-spastic medications, and pain management protocols. This documentation allows for the evaluation of potential confounding factors and ensures that biomarker changes can be interpreted in the context of treatment.

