### Justification of sample size

The study includes a total of 40 participants distributed as follows: 20 patients with spinal cord injury (SCI), 10 patients with traumatic brain injury (TBI), and 10 healthy controls. The selection of 20 SCI patients is based on the annual admission rates for SCI at the study institution, ensuring a representative sample of the population served. The inclusion of 10 TBI patients is justified to account for potential confounding factors arising from the overlapping but distinct injury mechanisms of SCI and TBI. Furthermore, 10 healthy controls are included to provide a robust baseline for sodium channel fragment levels, facilitating a balanced comparison across the three groups.

This sample size is sufficient to detect meaningful trends and associations between sodium channel fragments and clinical outcomes, including spasticity, while maintaining feasibility within the scope of a pilot study. The findings will generate preliminary evidence regarding the diagnostic and prognostic utility of sodium channel fragments in neurological injuries and will guide the design of larger-scale clinical trials.

Given the exploratory nature of this study, no formal interim analyses are planned. As the trial involves minimal-risk procedures, such as blood sampling, no pre-specified stopping rules have been established. In the event of significant deviations from the protocol or unforeseen safety concerns, the trial steering committee will consult the Ethics Committee to determine whether adjustments or study termination are necessary. All such decisions will be transparently documented and communicated to relevant stakeholders, including regulatory authorities, to ensure compliance with ethical standards.

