### Statistical methods

The primary objective of this study is to quantify sodium channel fragments in blood samples and compare their levels across the three participant groups: healthy controls (Group 1), SCI patients (Group 2) and TBI patients (Group 3). To address this objective, statistical analyses will begin with group comparisons.

1**Group Comparisons:** For normally distributed data, one-way analysis of variance (ANOVA) will be employed to identify differences in sodium channel fragment levels among the three groups. If data are not normally distributed, the Kruskal-Wallis test will be applied as a non-parametric alternative. Post-hoc analyses will follow these tests to assess pairwise comparisons, using Tukey’s test for ANOVA or the Mann-Whitney U test for non-parametric data.2**Effect Size Calculation:** Effect sizes (e.g. Cohen’s d for t-tests or η² for ANOVA) will be calculated to quantify the magnitude of differences between groups.

For secondary outcomes, analyses will focus on the temporal kinetics of sodium channel fragments and their correlation with clinical outcomes.

1**Temporal Kinetics:** Changes in fragment levels over time, measured at baseline (6 hours), during the acute phase (Days 1, 3, 5, 7), and at follow-up (Months 3 and 6), will be analyzed using repeated-measures ANOVA for normally distributed data. For non-normally distributed data, the Friedman test will be used. Bonferroni corrections will be applied during multiple comparisons.2**Spasticity Correlation:** The relationship between sodium channel fragment levels and spasticity severity in SCI patients will be assessed using Spearman’s rank correlation coefficients, with spasticity evaluated at Months 3 and 6 using the Modified Ashworth Scale (MAS).3**Subgroup Analysis (SCI Severity):** Subgroup analyses will investigate whether sodium channel fragment levels differ by injury severity. In SCI patients, severity will be categorized based on the American Spinal Injury Association (ASIA) Impairment Scale grades (A–D). Similarly, spasticity onset will be analyzed as a binary outcome (presence vs. absence). For TBI patients, the Glasgow Coma Scale (GCS) will be used to classify injury severity, enabling comparisons of sodium channel fragment levels across defined severity subgroups.

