Additional statistical methods will include multivariable linear regression models to adjust for potential confounders, including age, sex, injury severity (ASIA grades A–D for SCI, GCS scores for TBI), and concurrent medications (antispasmodics, analgesics, antiepileptics) as primary factors, as well as additional variables from Table 3 such as comorbidities (diabetes, organ failure), trauma context (type of accident), and biological parameters (hemoglobin, renal clearance) where statistically significant or clinically relevant, informed by prior literature [14,21]. This ensures that observed associations between sodium channel fragment levels and outcomes such as spasticity are robust and not influenced by baseline characteristics. Receiver operating characteristic (ROC) curves will be generated to identify threshold levels of sodium channel fragments that differentiate SCI from TBI or predict spasticity onset. To address missing data, multiple imputation methods will be applied, minimizing bias and preserving the validity of the analyses.

Continuous variables will be expressed as means with standard deviations for normally distributed data or medians with interquartile ranges for non-normally distributed data. Categorical variables will be summarized as frequencies and percentages. For all primary and secondary analyses, a two-tailed p-value < 0.05 will be considered statistically significant. Patients who die before the 3-month follow-up will be excluded from spasticity-related analyses due to insufficient time for spasticity development, but all data collected up to the time of death will be included in secondary analyses, such as demographic characterization and early biomarker levels.

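### With 10 TBI and 20 SCI patients and eight serial draws, the promise that multiple imputation preserves validity is unsupported; a mixed model on all available samples would serve the kinetics analysis better

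*Protocol article*

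**What the plan says.** The Statistical methods section handles missing data in one sentence: "To address missing data, multiple imputation methods will be applied, minimizing bias and preserving the validity of the analyses". The only other rule is that patients who die before Month 3 are left out of the spasticity analyses, while their earlier data are kept for other summaries.

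The methods this has to serve are set out in the same section.
- Group comparison: "For normally distributed data, one-way analysis of variance (ANOVA) will be employed", followed by Tukey's test. Kruskal-Wallis and Mann-Whitney are the alternatives if the data are not normal.
- Kinetics: repeated-measures ANOVA, with a fallback: "For non-normally distributed data, the Friedman test will be used".
- Spasticity in SCI patients: Spearman correlation with the Modified Ashworth Scale at Months 3 and 6.
- Multivariable linear regression, adjusted for "age, sex, injury severity (ASIA grades A–D for SCI, GCS scores for TBI), and concurrent medications (antispasmodics, analgesics, antiepileptics) as primary factors", and optionally for "comorbidities (diabetes, organ failure), trauma context (type of accident), and biological parameters (hemoglobin, renal clearance) where statistically significant or clinically relevant".

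The Justification of sample size section gives "20 patients with spinal cord injury (SCI), 10 patients with traumatic brain injury (TBI), and 10 healthy controls". SCI and TBI patients are sampled within 6 hours, on five acute-phase days and at Months 3 and 6. For TBI the text reads "Additional samples are obtained during the acute phase at Days 1, 3, 5, 7 and 14". That makes eight draws per patient.

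**The concern.** The sentence does more than name a method. It states a result: bias is minimised and validity is preserved. An analysis plan that is not shown could supply the imputation model, but it could not make that result hold whatever model is chosen at these group sizes.

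Two features work against it. First, the variables the article itself lists are numerous relative to 10 and 20 patients, so an imputation model using them is either unstable or cannot be fitted. Second, the kinetics tests need every patient to have every time point, so missing samples have to be filled in or patients dropped. If the fallback rank tests are used, there is no direct way to merge several imputed data sets into one test. At these sizes, one or two extreme imputed values could decide a kinetics or correlation result.

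**Working it through.** The article gives no missing-data rate, SD or correlation, so there is no stated figure to reproduce. Rates and correlations below are assumptions.

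**1. Coefficients needed to impute one draw by linear regression**
- Other draws only: 1 intercept + 7 draws = 8.
- TBI with primary factors: 8 + age 1 + sex 1 + GCS 1 + three drug classes 3 = 14, against 10 patients.
- SCI with primary factors: 8 + 1 + 1 + ASIA grade + 3. This is 14 if ASIA is entered as a linear score (1) and 16 if as four categories (3), against 20 patients.
- Adding the Month 3 and Month 6 outcomes: 16 in TBI, 16 to 18 in SCI.
- Adding the five optional covariates as well: 21 in TBI, 21 to 23 in SCI.

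**2. Residual degrees of freedom = patients − missing − coefficients**
- TBI, draws only, 1 missing: 10 − 1 − 8 = 1.
- TBI, draws only, 2 missing: 10 − 2 − 8 = 0, not estimable.
- SCI, 14 coefficients, 3 missing: 20 − 3 − 14 = 3.
- SCI, 16 coefficients, 4 missing: 20 − 4 − 16 = 0, not estimable.

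The TBI failure is easy to reach. If each sample is independently missing with probability 5%, a given time point has at most one of 10 missing with probability 0.95^10 + 10 × 0.05 × 0.95^9 = 0.914. The chance that at least one of eight time points has two or more missing is 1 − 0.914^8 = 51%. At 10% missing it is 91%.

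**3. Size of the instability** (4,000 simulated runs; eight equally correlated draws, correlation 0.5; one draw imputed by Bayesian normal regression; absolute error in SD units)

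| Case | Median | 90th percentile |
|---|---|---|
| TBI, 1 missing, draws only | 2.1 to 2.3 | 12.7 to 13.6 |
| SCI, 3 missing, 14 coefficients | 1.7 to 1.75 | 5.4 to 5.5 |
| True prediction model known | about 0.7 | about 1.75 |

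Ranges are across repeat runs.

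**4. What a small model does** (600 runs, 20 imputations, 20% missing completely at random, true correlation 0.5; Pearson correlation pooled on the Fisher z scale as a stand-in for Spearman)

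| Patients | Coefficients | Coverage, imputed | Width, imputed | Width, complete cases |
|---|---|---|---|---|
| 20 | 5 | 0.94 | 1.10 | 1.09 |
| 20 | 14 | 0.95 | 1.27 | 1.09 |
| 20 | 18 | not estimable | – | – |
| 10 | 5 | 0.97 | 1.84 | 1.75 |
| 10 | 8 | not estimable | – | – |

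The 5-coefficient model corresponds to an intercept, two adjacent draws, severity and age. It works in both groups, but gains no precision over complete cases.

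**5. Complete rows without imputation**

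The share of patients with all eight samples is (1 − d)^8 for per-sample missingness d.
- d = 5%: 66%, or 13.3 of 20 SCI and 6.6 of 10 TBI patients.
- d = 10%: 43%, or 8.6 and 4.3.
- d = 20%: 17%, or 3.4 and 1.7.

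Repeated-measures ANOVA and Friedman would be left with these patients. A mixed model keeps every observed sample.

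**6. Combining imputed data sets**

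The usual rule takes an estimate and its standard error from each data set: total variance = within + (1 + 1/m) × between. Kruskal-Wallis, Mann-Whitney and Friedman, used as tests, return a statistic and a p-value, so the rule does not apply directly.

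**The case against.** The strongest reply is that the article states no imputation model. The count of 14 to 16 coefficients is what its listed variables would imply if all were used, not something it commits to. The predictor list and pooling rule commonly belong in an analysis plan, so their absence is not a fault. This stands, and it limits the point.

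Other choices compatible with the same sentence also remove most of the instability in step 3. Using one summary of the patient's other draws gives a median error of 0.80 SD and a 90th percentile of 2.15 SD (TBI, 1 missing). Predictive mean matching on all the other draws gives 0.92 and 2.25 SD. Error in a single imputed value is also not the measure of validity; coverage is, and at 14 coefficients in SCI it was 0.95, at the price of wider intervals.

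The kinetics paragraph lists seven time points, omitting Day 14. On that count two missing TBI values leave 10 − 2 − 7 = 1 degree of freedom. That is estimable, but still poor: median error 2.2 SD, 90th percentile 13.9 SD.

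Three further inferences are tempting and not supported.
- That most planned tests are rank tests: parametric tests come first, and Kruskal-Wallis, Mann-Whitney and Friedman are fallbacks. Spearman is the only named test that is rank-based in every case, and it can be pooled after a Fisher z transformation.
- That imputation is prescribed for every analysis: the article does not say so, and it excludes early deaths from the spasticity analyses.
- That the regressions are affected by the pooling problem: the usual combining rule applies to them directly.

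**Conclusion.** The point holds in limited form. The unqualified assurance is unsupported for groups of 10 and 20 with eight draws: whether imputation behaves well depends entirely on keeping the model small. For the kinetics, the stated combination of complete-row tests and imputation is inferior to a method that needs neither imputation nor pooling.

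A reader might go further and conclude that multiple imputation cannot be valid here. The documents and the calculations do not support that: a 5-coefficient model gave near-nominal coverage in both groups. That result assumes data missing completely at random; informative missingness was not tested.

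The error sizes rest on an assumed correlation of 0.5 and an unpenalised regression on all other draws within each group. The complete-row shares rest on assumed independent missingness of 5% to 20% per sample. The coefficient counts use only the article's own variables. For an exploratory pilot this is a worthwhile, inexpensive correction to the analysis; it does not threaten the design.

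**What to change.** In the Statistical methods section:
- Analyse fragment kinetics with a likelihood-based linear mixed model on all available samples, without imputation: a patient random effect, time as a factor, log-transformed levels if skewed, and small-sample degrees of freedom. This replaces repeated-measures ANOVA and Friedman.
- Run the rank tests and Spearman correlations on available patients, and state the number in each.
- Confine any imputation to missing covariates in the regressions, with a short predictor list, and report it as a sensitivity analysis.
- Remove the claim that bias is minimised and validity preserved.

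The cost is analysis wording only; no sample, visit or patient number changes. Some tests will use fewer patients than were enrolled. The mixed model relies on a simple covariance structure and on data missing at random, and both should be stated as assumptions.

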### Ethical approval and dissemination policy

#### Research ethics approval.

The SpasT-SCI-T clinical trial adheres to the Declaration of Helsinki and the French Public Health Code. It received approval from the Comité de Protection des Personnes Est III (CPP number 2024-A00265-42) on October 7, 2024, and authorization from the National Agency for Medicines and Health Products (ANSM) on July 10, 2017. The trial is registered on Clinicaltrials.gov (NCT06532760). As a category 2 interventional study under French law, it involves minimal risk. Reporting follows the SPIRIT guidelines, with SPIRIT and CONSORT checklists provided (S1 and S2 Checklists).

#### Protocol amendments.

Any modifications to the trial protocol, including changes to eligibility criteria, outcome measures, or analytical methods, will be promptly communicated to all relevant stakeholders. These include the investigators, the Ethics Committee (CPP), regulatory authorities such as the ANSM (Agence Nationale de Sécurité du Médicament), and trial participants, when applicable. Updates will also be reflected in trial registries (e.g., ClinicalTrials.gov) and disseminated through publications and conference presentations as needed. All amendments will undergo prior review and approval by the CPP to ensure continued ethical compliance and transparency.

#### Data confidentiality and management.

Participant confidentiality is prioritized throughout the trial. All data are pseudonymized, and unique patient identifiers are used for sample tracking and clinical data management. Personal identifying information will not be associated with biological samples or research databases. Data will be securely stored in a password-protected electronic Case Report Form (eCRF) developed using REDCap, hosted on encrypted servers at Assistance Publique–Hôpitaux de Marseille (AP-HM). Access to the eCRF is restricted to authorized personnel, including the principal investigators and the designated data management team, through encrypted login credentials. Data integrity is ensured through daily backups, and all procedures comply with the European General Data Protection Regulation (GDPR). At the conclusion of the trial, all biological samples will be destroyed, and the pseudonymized data will be archived securely for 15 years, as mandated by French regulations.

#### Ancillary and post-trial care.

As the trial involves minimal-risk procedures, participants are not expected to require ancillary or post-trial care related to their involvement. In the event of harm directly resulting from study participation, liability insurance provided by the sponsor ensures coverage. Participants will retain access to their treating physicians for medical concerns during and after the trial.

#### Dissemination plan.

The results of the SpasT-SCI-T clinical trial will be disseminated through peer-reviewed journals, conference presentations, and publicly accessible databases. The findings will adhere to CONSORT guidelines to ensure transparency and rigor in reporting. Participants who express interest in the study’s results will be provided with an aggregated summary by the investigators, in compliance with French regulatory requirements. To maintain confidentiality, no individual results will be disclosed. Authorship of publications will follow the guidelines of the International Committee of Medical Journal Editors (ICMJE), ensuring that all contributors to the study design, conduct, analysis, and reporting are appropriately credited.

#### Baseline data.

Baseline data were systematically collected to characterize the study population and ensure comparability across the three participant groups (healthy controls, SCI patients, and TBI patients). Key baseline variables are presented in a detailed summary table to promote transparency and support balanced comparisons between groups.

## Discussion

### Rationale

The present clinical trial aims to validate sodium channel fragments generated by calpain as biomarkers for assessing injury severity and prognosis in SCI and TBI, and to predict spasticity outcomes. CNS injuries initiate a cascade of molecular events, including calcium overload and calpain activation, leading to the proteolysis of Nav1.6 sodium channels (Fig 3). These cleavage products emerge as detectable blood biomarkers, offering a window into injury severity and secondary complications like spasticity. The SpasT-SCI-T trial builds on evidence linking calpain activity to spasticity severity [21], hypothesizing that sodium channel fragments can serve as reliable prognostic markers for functional outcomes in SCI and TBI. This aligns with the growing need for biomarkers to enhance CNS injury management, from understanding disease progression to guiding clinical decisions [14,15,52].

**Fig 3 pone.0319635.g003:**
[figure not shown]
Calpain activation following spinal cord injury. Traumatic injury to the spinal cord triggers glutamate release into the extracellular space, causing a sustained increase in intracellular calcium concentrations in motoneurons. This calcium influx activates calpain, a calcium-dependent protease, which cleaves Nav1.6 voltage-gated sodium channels. The cleavage results in an upregulation of persistent sodium currents (I_NaP_), contributing to motoneuron hyperexcitability and the development of spasticity. Additionally, fragments of cleaved sodium channels accumulate in the sublesional spinal cord and can be detected in the bloodstream. These fragments represent a promising biomarker for assessing SCI severity and predicting spasticity outcomes.

### Comparison with previous biomarkers

Previous studies have explored calpain-mediated α-II spectrin fragments as indicators of SCI severity [52]. However, their utility is limited by several factors: spectrin is also cleaved by caspase-3 during apoptosis, reducing its specificity to calpain activity [53]; its expression is transient, restricting its use to the acute phase [15]; and its abundance in red blood cells complicates interpretation in polytrauma cases [52]. In contrast, sodium channel fragments offer distinct advantages. Exclusively expressed in the nervous system and resistant to caspase-3 cleavage [37], they provide greater specificity. Moreover, preliminary data suggest they persist beyond the acute phase, enabling long-term monitoring of spasticity and recovery, attributes that address critical gaps in current biomarker options.

